**Fig. 4 Fig4:**
[figure not shown]
Study assessments timepoints. Patients will be randomized into 2 arms after completion of the G8 screening phase; Arm A; will be evaluated by Comprehensive Geriatric Assessment (CGA) at baseline and would be re-evaluated after every 6 months and If necessary, an onco-geriatric follow-up will be carried out. Arm B is the Control group, no geriatric visit is scheduled. Both arms will be evaluated for their quality of life using EORTC – QLQ-C30 questionnaire every 3 months. Blood samples from patients will be collected to evaluate T cells senescence and myeloid-derived suppressor cells at baseline and after 12 months or at disease progression

### Biological study

The study is designed to evaluate T senescent cells and MDSC, and their modifications with treatment, in the peripheral blood of patients enrolled in the ONCO-aging study; blood samples will be collected at baseline (before start of therapy) and at the time of disease progression.

Blood samples (10 ml whole blood in Vacutainer EDTA tubes) are processed and analysed at the Immuno-Oncology Laboratory, at the Center for Translational Research on Autoimmune & Allergic Diseases – UPO-CAAD, in Novara, IT.

Peripheral mononuclear blood cells (PBMCs) are collected and isolated by Ficoll/Hypaque density gradient. T CD3 + Lymphocytes are isolated from the PBMCs by magnetic beads. The following markers will be tested by reverse transcription quantitative PCR, according to a manufactory protocol: p16INK4a and p21Cip/Waf1.

The Enzyme-Linked ImmunoSorbent Assay (ELISA) is used to evaluate the expression of cytokines and chemokines (e.g. CCL2/MCP-1, IFNγ, IL-6, IL-8), in plasma obtained from the same blood samples.

MDSC analysis is performed by flow cytometry in PBMCs. Assessment of MDSC phenotype is characterised by using the following markers: for monocytes-MDSC CD14^+^HLA-DR^+^, and for granulocytes-MDSC CD15^+^CD33^int^ and LOX-1^+^. Biological markers for T cell senescence and MDSC characterization are detailed in Table 1.

**Table 1 Tab1:** Senescent T cells and Myeloid Derived Suppressor Cell subtypes markers

Type of cell	Markers
Senescent T cell	CD28- (co-stimulatory) CD57+ (senescence) KLRG1+ (senescence) p16INK4 (senescence) p21Cip/Waf1 (senescence)
M-MDSC	CD14+ (monocyte differentiation) CD11b+ (migration) HLA-DR^low/−^ (proliferation) CD15- (migration)
PMN-MDSC	CD14- (monocyte differentiation) CD11b+ (migration) HLA-DR+ (proliferation) CD15+ (migration) CD33^int^ (adhesion) LOX-1+ (proliferation)

Legend-*CD* Cluster of Differentiation; *PMN-MDSC* PolyMorphoNucler-Myeloid Derived Suppressor Cell; *M* Monocytic-Myeloid Derived Suppressor Cell; *LOX-1* Lectin-like OXidized low-density lipoprotein (LDL) receptor-1

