### Study Design

The ONCO-Aging study is a prospective, randomized study and includes a clinical trial and a collateral biologic study. Patients older than 65 years, with hematological or oncological neoplasms, who refer for treatment to the Oncology, Hematology and Radiation Oncology Divisions of the University Hospital Maggiore della Carità in Novara, IT, and candidate to therapies with innovative target directed agents or to combined schedules including RT and CT, are screened for frailty by the G8 questionnaire; according to previous evidence, a score ≤ 14/17 is considered the threshold for frailty [16, 17]. Targeted directed agents include the following drugs: tyrosine-kinase inhibitors (TKis), monoclonal antibodies and immune checkpoint inhibitors (ICIs), alone or in combination schedules with CT. Combined treatment schedules including RT and CT are also included. Patients with a G8 score ≤ 14/17, are randomized in a 1:1 ratio to the following procedures: arm A, onco-geriatric evaluation by CGA; arm B, standard clinical care, according to local practice. Figure 1 shows the flowchart of the study. Patients are randomized by a REDCap dedicated system. Patients assigned to arm A undergo a CGA at baseline, before treatment start and every 6 months thereafter and may receive a CGA based geriatric intervention if required according to the geriatrician judgement (Fig. 2). Patients in arm B are managed according to clinical practice (Fig. 3). Blood samples to assess the prognostic and predictive value of cell-derived data (MDSC and T cell senescence) and their modification with treatment, will be collected at baseline and at the time of disease progression. Blood samples from healthy, age-matched controls, are recruited on a voluntary basis and also from the UPO Biobank.

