### Objectives

The primary objective of the ONCO-Aging study is to assess the impact of the CGA and related interventions on the Quality of Life (based on the EORTC QLQ C30 questionnaire) of onco-hematological patients, with a G8 score ≤ 14/17, candidate to innovative target agents or integrated RT and CT schedules. Secondary objectives: *1.* to assess the percentage of treatment modifications, due to toxic events, in those patients who receive CGA assessment and related interventions, compared with those treated according to local clinical practice; 2) to evaluate the impact of CGA and related interventions on patient outcome and treatment adherence, as compared to those in the control arm.

The aim of the biological study is to assess the presence and the modifications induced by treatments of senescent T cell and MDSC in the peripheral blood of enrolled patients in both arms to evaluate the correlation with treatment efficacy and patient characteristics, including comorbidities, concomitant drugs, and lifestyle habits.

The primary endpoint is Health Related Quality of Life, based on the EORTC QLQ C30 questionnaire [18]; EORTC QLQ C30 questionnaire will be administered at baseline and every 3 months during treatment/follow up.

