### Study procedures

Comprehensive Geriatric Assessment (CGA): in arm A, patients receive a dedicated geriatric examination (60–90 min), administered by a dedicated geriatrician, and are classified according to CGA results and the Rockwood Frailty Index (RFI) as “frail” (RFI > 0.25), “unfit/prefrail” (0.08 > RFI < 0.25) or “fit” (< 0.08) [19].

The CGA includes evaluation of cognitive status with the Mini Mental State Examination (MMSE), Clock drawing test (CDT), and Montreal Cognitive Assessment (MOCA) [20]; of psychosocial status by the means of Geriatric Depression Scale (GDS) and Social Vulnerability Index (SVI) [21]; of disability by Activities of Daily Living (ADL) and Instrumental Activities of Daily Living (IADL) [22, 23]; of nutritional status by Mini Nutritional Assessment (MNA) [24]; of comorbidities by Cumulative Illness Rating Scale for Geriatrics (CIRS-G) and of pharmacological impact by number of drugs [25]; of sarcopenia and physical performance by Hand Grip Strength, Timed Up and Go test, Tinetti Scale, and number of falls in last six months [26]. CGA is performed at baseline and every 6 months. If issues are found in the areas of fragility, mid-term evaluations are foreseen, as indicated by the geriatrician. CGA based interventions will cover nutritional imbalance, social issues including the availability of caregiver and psychological interventions by dedicated psyco-oncologists.

In both arms, QoL assessment by the standardized EORTC QLQ-C30 questionnaire is performed at baseline (before treatment start) and every 3 months. Disease evaluation is performed in both arms according to local clinical practice. Patients are observed for up to 12 months or until disease progression (Fig. 4).

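### The protocol article gives two rules for the second research blood sample; under the progression-only rule, marker change cannot be compared between patients who progress and those who do not

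*Protocol article*

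**What the plan says.** The protocol article describes the timing of the second blood sample in three places.

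- Study Design: samples "will be collected at baseline and at the time of disease progression".
- Biological study: "blood samples will be collected at baseline (before start of therapy) and at the time of disease progression".
- Fig. 4 legend: sampling for T-cell senescence and MDSC takes place "at baseline and after 12 months or at disease progression".

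The first two name no later sample other than the one at progression. The third adds month 12. No statement gives one of them precedence.

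Two further statements matter. Study procedures sets the observation window: "Patients are observed for up to 12 months or until disease progression". Objectives sets the aim of the biological study for both arms: "to assess the presence and the modifications induced by treatments of senescent T cell and MDSC in the peripheral blood of enrolled patients", and then "to evaluate the correlation with treatment efficacy and patient characteristics".

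**The concern.** A patient who reaches month 12 without progressing is an ordinary outcome under the observation window. The two rules treat that patient differently: Fig. 4 provides a second sample, while Study Design and Biological study do not.

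If the progression-only rule is followed, having a second measurement depends on treatment having failed. Two things are lost. Change in the markers cannot be compared between patients who progressed and patients who did not. And because every follow-up measurement is made at progression, change caused by treatment is confounded with change caused by the advancing disease. The article's own Discussion lists both the cancer and its treatment among the causes of immune senescence, so this confounding follows from the trial's stated rationale.

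The aim at stake is the part of the biological study that concerns change under treatment and its relation to efficacy. A month-12 sample that is not taken cannot be recovered later, and the Trial status section reports 63 patients already randomised.

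**Working it through.** **Step 1. The plan's own figure.** The only sample size stated is for the quality-of-life endpoint. Inputs from Statistical design: two-sided alpha 0.05, power 0.80, difference 10, SD 20, 10% loss.

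- Effect size: 10/20 = 0.5.
- Two-sample t-test: 63.8, rounded up to 64 per arm.
- Inflation for loss: 64/(1 − 0.10) = 71.1, rounded up to 72 per arm, or 144 in total.

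This matches the stated 144. It serves below only as the number of randomised patients; no figure is stated for the biological study.

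**Step 2. The two rules side by side.** Fig. 4 is read as progression, or month 12 if progression has not occurred, which fits the observation window.

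| Patient's course | Study Design and Biological study | Fig. 4 legend |
|---|---|---|
| Progresses by month 12 | Baseline and progression | Baseline and progression |
| Reaches month 12 without progressing | Baseline only | Baseline and month 12 |

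The rules differ only in the second row. Under the progression-only rule the number of non-progressors with a measured change is zero, whatever the progression rate.

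**Step 3. How many patients fall in the second row.** The documents give no progression rate or median, so this is an assumption. With exponential progression, the proportion progression-free at 12 months is 0.5^(12/median).

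- Median 6 months: 0.5^2 = 0.25, and 0.25 × 144 = 36.
- Median 12 months: 0.5^1 = 0.50, and 0.50 × 144 = 72.

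Without the exponential form, assume directly that 30% to 80% progress within 12 months.

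- 30% progress: 0.30 × 144 ≈ 43 have a second sample and about 101 do not.
- 80% progress: 0.80 × 144 ≈ 115 have a second sample and about 29 do not.

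These counts ignore death and loss to follow-up. With the planned 10% loss, about 130 remain (144 × 0.90 = 129.6), and the 25% to 50% range becomes about 32 to 65.

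**Step 4. What each rule leaves estimable.**

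- Baseline marker levels against efficacy: available in all sampled patients under either rule.
- Change against time to progression or response within progressors: available under either rule, in a group selected by outcome.
- Change in progressors compared with change in non-progressors: available only under the Fig. 4 rule.
- Treatment-induced change separated from progression or time on treatment: not secured by either rule. Under Fig. 4, non-progressors are sampled at month 12 and progressors at progression, usually earlier, so sampling time is determined by outcome.

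**The case against.** The harm exists only if the progression-only wording governs. Fig. 4 is the figure devoted to assessment timepoints, and Study procedures refers to it when setting the observation window, so the other two statements may simply be short forms of it. The SPIRIT schedules in Figs. 2 and 3 list both month 12 and progression among their abbreviations; their images are not shown and may settle the matter. This stands as a limit: a reader might infer that non-progressors are in fact going unsampled, and the documents do not show that. They show three written statements that disagree and no rule of precedence.

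A reader might also infer that, under the progression-only rule, the markers cannot be related to efficacy at all, or that outcome does not vary among the sampled patients. That goes too far. Baseline levels exist for everyone sampled, progressors differ in time to progression and may differ in response, and the Discussion's interest in age, immune senescence and frailty does not require a second sample. The loss is confined to marker change across the whole cohort.

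It is also fair to say that adopting Fig. 4 does not cure everything. Adjusting for time since baseline would not help, because the two groups have almost no overlap in sampling time and the adjustment would rest on extrapolation.

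Finally, this is a collateral study in a trial that describes itself as exploratory and single-centre. That limits the weight of the point but does not remove the contradiction.

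**Conclusion.** The inconsistency is established from the text. Following Study Design and Biological study as written would leave no marker change in any patient who is progression-free at month 12, which undercuts the aim of assessing change under treatment and relating it to efficacy. That conclusion holds at any progression rate.

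The number affected cannot be derived from the documents. The figure of 36 to 72 of 144 is illustrative and rests on exponential progression, an assumed median of 6 to 12 months, and no allowance for dropout or death. The trial enrols a mix of advanced solid tumours and haematological cancers at any stage, and the article offers no support for a particular median.

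Randomisation, the sample size and the quality-of-life primary endpoint are unaffected. The point should be corrected, but it does not threaten the main trial.

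**What to change.** 1. Reconcile Study Design and Biological study with Fig. 4, so that all three say that the second research sample is taken at progression, or at month 12 if the patient has not progressed.
2. Report marker change separately for patients who progressed and patients who had not progressed by month 12, with the sampling time shown for each group. Do not rely on an adjustment for time since baseline.
3. State that sampling time is tied to outcome, so that a difference in change between the two groups is descriptive and is not evidence of prognostic or predictive value. Baseline levels remain the usable predictors of efficacy.

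If Fig. 4 is already the working rule, the cost is wording. If the progression-only rule is being followed, the cost is one additional research blood draw at month 12 in non-progressors. Month 12 is already a listed timepoint in both arms.

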**Methods:**

Patients aged > 65 years, candidate to target directed agents or to RT + CT treatments are screened for frailty by the G8 test; those patients classified as frail (G8 ≤ 14) are randomized to receive a CGA at baseline or to conventional care. The primary endpoint is QoL, assessed by EORTC QLQ-C30C. As collateral biological study, the potential prognostic/predictive role of T-cell senescence and myeloid derived suppressor cells (MDSC) are evaluated on plasma samples.

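### Monocytic MDSC are HLA-DR positive in the Biological study text but HLA-DR low or negative in Table 1, so one definition must be fixed for that subset

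*Protocol article*

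**What the plan says.** The Biological study section of the protocol article describes the MDSC assay: "MDSC analysis is performed by flow cytometry in PBMCs". The next sentence gives the phenotypes. The monocytic subset is written "for monocytes-MDSC CD14^+^HLA-DR", and the HLA-DR there carries a superscript plus sign. The granulocytic subset follows, as CD15+, CD33 intermediate and LOX-1+.

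The text then hands over to the table: "Biological markers for T cell senescence and MDSC characterization are detailed in Table 1". In Table 1 the M-MDSC row starts with CD14+ and CD11b+ and ends "HLA-DR^low/−^ (proliferation) CD15- (migration)". The PMN-MDSC row starts with CD14- and CD11b+ and ends "HLA-DR+ (proliferation) CD15+ (migration) CD33^int^ (adhesion) LOX-1+ (proliferation)". Table 1 thus gives HLA-DR+ to the granulocytic subset and not to the monocytic one.

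The Objectives section sets out what the measurement is for: the presence of these cells in blood, their change with treatment, and their correlation with treatment efficacy and patient characteristics.

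**The concern.** The same subset carries two HLA-DR entries in the same section, and nothing there says that one replaces the other. Among CD14+ cells, HLA-DR is the only marker in the text's definition that narrows the monocytic subset further, so its sign decides which cells are counted.

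If the text's version were followed, the reported M-MDSC frequency, its change during treatment, its correlations and any comparison with the healthy controls would refer to cells that Table 1 largely leaves out. This would be an error of definition and not of precision, so enrolling more patients would not reduce it. The Discussion says that the results will feed a larger multicentre study, so an unclear definition could be carried into that study.

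**Working it through.** The point involves no arithmetic. The check is to set the two definitions side by side.

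**Monocytic subset**

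| Marker | Running text | Table 1 | Relation |
|---|---|---|---|
| CD14 | + | + | agree |
| HLA-DR | + | low/negative | conflict |
| CD11b | not given | + | shorter text, no conflict |
| CD15 | not given | - | shorter text, no conflict |

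**Granulocytic subset, as a control on how the text relates to the table**

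| Marker | Running text | Table 1 | Relation |
|---|---|---|---|
| CD15 | + | + | agree |
| CD33 | intermediate | intermediate | agree |
| LOX-1 | + | + | agree |
| CD14, CD11b, HLA-DR | not given | -, +, + | shorter text, no conflict |

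The text names two markers for the monocytic subset and three for the granulocytic, five in all. Four agree with Table 1 and one does not. The text therefore behaves as a short form of the table everywhere except at HLA-DR for the monocytic subset.

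**What the conflict does to the count.** Take CD14+ cells that also meet the CD11b and CD15 entries of Table 1 and sort them by HLA-DR:

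| HLA-DR expression | Counted under the text? | Counted under Table 1? |
|---|---|---|
| negative | no | yes |
| low | depends on where positivity begins | yes |
| high | yes | no |

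The definitions disagree on the first and third rows. On the second they may overlap.

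**Could it be an artefact of reading the PDF?** This is unlikely. The superscripts plus, intermediate and low/negative all survive in this section, including the plus on the HLA-DR in question.

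**How many samples could be involved?** Trial status reports 63 patients randomised when the article was written, and blood is drawn at baseline. Samples from at most 63 patients could therefore have been processed by then, plus any from healthy controls. The article does not say how many had been, or under which definition.

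**The case against.** The strongest reply is that the article itself shows which definition is meant. The text sends the reader to Table 1 for detail, and Table 1 gives the complete four-marker phenotype where the text gives two. On that view the plus sign is a slip, and the laboratory, working from its own procedures, has probably never used it. This is a good argument and it largely stands. It is also the reason why the correction can be made in the direction of Table 1. It does not remove the point: a methods section still states an incorrect or contradictory definition, and the article gives no confirmation of what the laboratory did.

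Three stronger readings are tempting, and the document does not support them.

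- A reader might infer that every sample, from up to 144 patients and the controls, has been or will be misclassified. That would require the laboratory to be working from this sentence, which the article nowhere says.
- A reader might infer that the two definitions exclude each other completely. The text names markers and sets no threshold, and Table 1 says low or negative, so dimly stained cells could satisfy both. The conflict is clear only for cells that are negative or high.
- A reader might infer that a numerical HLA-DR cut-off is missing. That is a laboratory detail which a journal article may leave to a fuller protocol or procedure.

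It is also fair to say that the reach is narrow. The MDSC work is collateral to the randomised comparison, the Discussion calls the trial exploratory, and only one of two MDSC subsets is affected.

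**Conclusion.** The contradiction is real, lies within one section and needs no outside source to establish. Following the text would define M-MDSC as a largely different population from Table 1. How far this has affected any data is unknown: the effect is nil if the laboratory already uses Table 1, and reaches all M-MDSC results of the collateral study if it uses the text.

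The primary endpoint (EORTC QLQ-C30), the sample size of 144, the intention-to-treat comparison and the secondary clinical objectives do not depend on this marker.

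The conclusion assumes that the sentence and the table describe the same assay, which the cross-reference between them supports. Preferring Table 1 rests on that cross-reference, on its fuller phenotype, and on the agreement of the other four shared entries.

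**What to change.** 1. Correct the running text so that monocytic MDSC carry the Table 1 phenotype (CD14+, CD11b+, HLA-DR low or negative, CD15-) and one definition applies throughout. This changes one line.
2. Ask the laboratory which definition it has applied to the samples analysed so far, and record the answer. This costs one query.
3. Only if the text's definition was used and the flow data were kept, reanalyse those data under Table 1. No new blood is needed for the HLA-DR correction, because CD14 and HLA-DR appear in both definitions. CD11b is named only in Table 1, so check that it was stained before claiming the full four-marker phenotype for those samples.

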## Discussion

Elderly patients present specific age-related conditions that may increase the risk of complications from anti-tumor therapy and compromise prognosis and QoL [7]. The ONCO-Aging trial is designed to assess whether the inclusion of a CGA and CGA based interventions, results into an amelioration of QoL, in onco-hematological patients receiving innovative target agents or treatment schedule including RT and CT. The study is dedicated to elderly patients with a G8 score ≤ 14/17. This aspect is particularly important in order to balance efficacy and tolerability of modern anticancer therapies, in particular TKis, ICIs and monoclonal antibodies, in old and frail patients, often excluded from registrative clinical trials, due to stringent inclusion criteria or physician fear of unexpected toxicities.

At present, most of the oncological and hematological treatments are established on the basis of the performance status (PS) evaluation, according to the World Health Organization (WHO) scale or to Eastern Cooperative Oncology Group (ECOG); this aspect is particularly evident in the inclusion criteria of clinical trials. However, this approach may not be enough to correctly evaluate an elderly patient, as severity of co-morbidities and frailty, may not directly correlate with PS alteration [27]. Thus, more specific functional scales, as those employed in the geriatric assessments, are needed to better define the clinical condition of elderly patients in the context of a CGA, with the aim to identify and separate elderly fit patients from those who are unfit. At present, there is no consensus on the exact definition of “unfit patient”, due to limited evidence, non-homogeneous inclusion criteria and inconsistent results.

From a biologic point of view, aging correlates with a progressive deterioration of the immune system in a process that is defined “immune senescence” [28], due to the associated functional decline of the immune system. Immune senescence is the result of many factors, including tissue damage, DNA damage, chronic inflammation, cell stress, cancer itself and anti-cancer treatments. In this context, an increasing number of T-cells and MDSC with a potential cytotoxic and suppressive activity, has been reported in observations from patients and preclinical data [29].

Likewise, it can be speculated that the biological age measured by the CGA and expressed in terms of fitness, unfitness and frailty could be related to a progressive inefficiency of the immune system, that might be predominant in frail patients. This hypothesis derives from the observation that in patients with solid and hematological malignancies, CGA-defined frail patients seem not to benefit from potentially life-saving therapies compared with younger counterparts [20]. Many studies provided evidence that the unfavorable outcome of elderly patients is partly related to clinical and biological differences in the disease itself, such as a more aggressive phenotype, more frequent advanced stage and presence of symptomatic disease [30]. To clarify this aspect, we added a biological aspect in our study to evaluate the role of T cell senescence and MDSC in our cohort of frail patients and to investigate the possible relationship among age, immune senescence and frailty.

Our trial has some limitations. It is a monocentric exploratory study, with a limited number of patients with different solid and hematologic tumors. The different types of diseases that can be included usually have different timepoints for the radiological and clinical evaluations, but as a starting protocol, we decided to identify standard timepoints visits for geriatric and radiologic evaluations, according to local clinical practice and guidelines. On the other side, given the network organization of the “Rete Oncologica Piemontese”, where the University Hospital Maggiore della Carità in Novara, IT, is the second most important hub in the region, and therefore is allowed to prescribe innovative oncological treatments and to perform aggressive combination therapies with the association of RT and CT, the probability of poor compliance or drop out during follow up is minimal. This eventuality is also further reduced by the regular introduction of palliative simultaneous care in frail patients of any age, being our center an ESMO designated center for simultaneous care. The results of the ONCO-aging study, dedicated to the elderly patient population, will be used to define a global strategy within the “UPO AGING project”, to improve our aging-specific research with a multicenter study including a larger number of patients and a more selective division by cancer type and treatments.

